**Sample size estimation:**

After the adjustments of epidemic prevention and control policy in Beijing, SCTV01E showed a VE of approximately 70%-77% in the real-world. A total of 59 symptomatic SARS-CoV-2 infection cases will provide approximately 90% power to detect a VE of 70% at one-sided type one error 0.025 among participants in the per-protocol set for efficacy (PPE).

The hypothesis of sample size for vaccine efficacy endpoint:

- The COVID-19 incidence rate per month in the control arm is about 1.5%
- The dropout rate during the study is about 10%
- The participants with positive results of PCR test at baseline or infection of SARS-CoV-2 within 7 days after the study vaccination should be excluded from the analysis of primary endpoint cases, which is about 15%

Based on the assumptions aforementioned, approximately 10,000 participants will be enrolled in this study. The final number of participants enrolled in the study will depend on the incidence of COVID-19 at the time of the enrollment and the accumulation of primary endpoint cases, and the actual enrolled sample size may vary accordingly. In addition, 5%-10% of participants will be involved in the immunogenicity subgroup.

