**H0:** The VE of SCTV01E versus control is  $\leq 30\%$ .

**H1:** The VE of SCTV01E versus control is  $> 30\%$ .

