|                                                     |                                                                                                                                                                                                                                                                                                                                                                                                                                                                                                                                                                                                                                                                                                                                                                    |
|-----------------------------------------------------|--------------------------------------------------------------------------------------------------------------------------------------------------------------------------------------------------------------------------------------------------------------------------------------------------------------------------------------------------------------------------------------------------------------------------------------------------------------------------------------------------------------------------------------------------------------------------------------------------------------------------------------------------------------------------------------------------------------------------------------------------------------------|
|                                                     | 
10) Secondary endpoint: among the population in PPE-14, VE for obvious symptomatic infection of SARS-CoV-2 14 days (<math>\geq 15</math> days) after the study vaccination is higher than 30%.
 
Interim and final analysis
 
The is no planned interim analysis in this study. The final analysis will be performed for the primary endpoint at the significance level of 0.025 unilateral when more than 59 primary endpoint cases have been collected. The final analysis will be performed by an independent third party, the sponsor will set up an unblinded team for delivery. Investigators, participants and team members directly involved in this study will remain blinded for long-term efficacy and safety follow-up.
 |

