## 4.2 Randomization

This clinical trial is a randomized and double-blind Phase III clinical trial. Participants will be randomized to the study vaccine group or the placebo group at a ratio of 1:1. To maintain relative balance between groups, participants will be stratified and randomized by age (18–59 years,  $\geq 60$  years), vaccine type of the last previous dose (inactivated, non-inactivated), and region (study site). Blind codes for participant randomization and blind codes for drug numbers will be generated and maintained by a third party.

Participants eligible for screening will be randomized by the Interactive Web Response System (IWRS) and vaccinated according to random numbers. For participants who withdraw from the study for any reason after randomization, regardless of whether they are administrated with the study

vaccine or not, their random numbers will be retained, and they shall not participate in the study again.

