### 4.3 Sample size

After the adjustment of Beijing epidemic prevention and control policy, the protective efficacy of SCTV01E is between 70% and 77% in the real-world study. Therefore, assuming a protective efficacy (VE) of 70% (Hazard Ratio = 0.3) for the PPE population (as defined in the Analysis Set section) 7 days post-vaccination, in the condition of 59 cases, there is approximately 90% power to reject the null hypothesis  $H_0$  at a one-sided Type I error level of 0.025. The following assumption will be considered for sample size estimation and approximately 10000 participants (adjusted for actual infection rates) will be included. The final number of participants enrolled depends on the actual infection rate and the cumulative number of COVID-19 events. Of these participants, 5%–10% will be included in the immunogenicity subgroup.

- In the control group, the symptomatic infection of SARS-CoV-2 within 1 month is about 1.5%.
- The dropout rate during the study is about 10%.
- Approximately 15% of participants could not be included in the assessment of the number of events after 7 days because they are PCR positive at baseline or have an infection within 0–7 days after vaccination.

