### **7.11 Interim analysis**

There will be no planned interim analysis plan for this study. The study will conduct a final analysis of the primary endpoint at a one-sided significance level of 0.025 when at least 59 target events for the primary endpoint have accumulated. This analysis will be performed by an independent third party and the sponsor will establish an unblinded submission team to complete the submission. Investigators, participants, and team members directly involved in the project will remain blinded for long-term protective efficacy and safety follow-up.

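### At the assumed 70% efficacy, 59 events give about 80% power for the planned Cox confidence-interval test, not the stated 90%

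*Combined protocol and SAP*

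**What the plan says.** The synopsis (Sample size estimation) says "A total of 59 symptomatic SARS-CoV-2 infection cases will provide approximately 90% power to detect a VE of 70" percent, "at one-sided type one error 0.025", among participants in the PPE. SAP 4.3 repeats this, "assuming a protective efficacy (VE) of 70% (Hazard Ratio = 0.3") for the PPE population, and says that "in the condition of 59 cases, there is approximately 90% power to reject the null hypothesis". The null in both documents is VE of 30% or less, a hazard ratio of 0.7 or more. SAP 4.2 sets the allocation: "Participants will be randomized to the study vaccine group or the placebo group at a ratio of 1:1". Under SAP 7.5 and 7.6.1, success means that the lower limit of the two-sided 95% interval for VE, taken from the Cox model, lies above 30%.

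The single efficacy analysis is triggered, in the protocol synopsis (Interim and final analysis), "when more than 59 primary endpoint cases have been collected" and, in SAP 7.11, "when at least 59 target events for the primary endpoint have accumulated".

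Neither document names the power formula or gives the expected split of cases by arm.

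**The concern.** The number 59 comes out exactly if the variance of the log hazard ratio is taken as 4/D, where D is the total number of events. That variance is right only when the two arms contribute similar numbers of cases. A vaccine that removes 70% of cases under 1:1 allocation cannot produce such a split: fewer than a quarter of the cases come from the vaccine arm. The interval from the fitted Cox model reflects the actual split, so it is wider than the formula allows.

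There is no interim analysis, so the primary claim is decided at one event-triggered look. The nine secondary tests in the fixed sequence can be made only if it succeeds. The stated power is therefore also the stated chance that any formal efficacy claim can be made.

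A smaller matter is that the two trigger sentences differ by one event, and neither says that the counted cases must be in PPE.

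**Working it through.** **Inputs.** One-sided alpha 0.025, so z = 1.960. Null hazard ratio 0.7 and assumed hazard ratio 0.3. Power 90%, so z = 1.2816. D = 59 events, allocation 1:1. These come from the synopsis (hypothesis and sample size) and SAP 4.2, 4.3 and 7.5. The 1.5% monthly incidence and 10% dropout affect how fast cases accrue, not the power at a fixed number of events.

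**Step 1: reproduce the plan's figure.** The distance from the null is |ln(0.3/0.7)| = 0.8473.

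- Events = 4 × (1.960 + 1.2816)² / 0.8473² = 58.54, rounded up to 59.
- Power at 59 = Φ(0.8473/√(4/59) − 1.960) = Φ(0.8473/0.260 − 1.960) = 90.2%.

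Both stated numbers are recovered. Two alternatives do not recover them: Freedman's formula with the same ratio gives 66 events, and testing against a hazard ratio of 1 gives 29.

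**Step 2: expected split of cases.** With equal arms and a low attack rate, the vaccine share of cases is HR/(1 + HR).

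- At HR 0.3: 0.3/1.3 = 0.231, so 13.6 vaccine and 45.4 placebo cases of 59.
- At the null, HR 0.7: 0.7/1.7 = 0.412, so the split is unequal even there.

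**Step 3: variance with that split.** 1/13.6 + 1/45.4 = 0.0955, against 4/59 = 0.0678. The standard error is 0.309 instead of 0.260.

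**Step 4: power at exactly 59 events, VE 70%.**

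| Method | Power |
|---|---|
| Formula with 4/D (reproduces the plan) | 90.2% |
| Wald formula: Φ(0.8473/0.309 − 1.960) | 78.3% |
| Exact conditional binomial: success needs 16 or fewer vaccine cases, actual alpha 0.018 | 81.5% |
| Simulated Cox model, upper Wald 95% limit of HR below 0.7; 3,825 per arm | 80.5% |
| The same; 1,300 per arm | 80.8% |
| Asymptotic score (normal approximation to the binomial) | 84.4% |
| Likelihood-ratio test on the case split | 88.3% |

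Each simulated figure rests on 20,000 runs with exponential event times, no stratification, and stopping at the 59th event. The 3,825 per arm is 10,000 × 0.90 × 0.85 / 2 from the plan's assumptions; 1,300 is close to the PPE arm sizes in Table S2 (1,309 and 1,314). Under the null, the simulated one-sided error of the Wald criterion was 1.7–1.8%.

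**Step 5: events needed for 90%.**

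- Wald formula: (1.960 + 1.2816)² / (0.231 × 0.769 × 0.8473²) = 82.4, so 83 events.
- Exact test: 92.0% at 75 events, 89.7% at 77 and 92.7% at 78. It stays above 90% from 78 onward.
- Simulated Cox Wald criterion at 78 events, 3,825 per arm: 92.4%.

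**The case against.** The fair case against has five parts.

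- **The sum is right.** The formula is standard and was applied correctly, and because the documents name no formula, its use is inferred. That stands as a description of where 59 came from. It does not make the stated power true for this design and this test.
- **The figure depends on the interval method.** The SAP says only that the interval comes from the model. Likelihood-based limits at 59 events reach 88%, but in simulation they carried a one-sided error of 3.0–3.3%, above the 2.5% the plan allows. At 59 events, no test evaluated with the actual split reaches 90%.
- **The analysis may contain more than 59 events.** Both triggers are minimums, and power moves in steps. From 60 to 63 events, a Wald limit on the case split gives 86.8%, 85.1%, 83.3% and 88.0%, with actual alpha of 0.0275 at 60 and 0.0266 at 63. The exact test gives 79.5%, 85.1%, 83.3% and 81.4%. So a slight overrun helps, but does not restore 90%.
- **The shortfall is specific to VE 70%**, the low end of the 70–77% range the plan cites. Exact power at 59 events is 93.3% at VE 75% and 96.1% at VE 77%. This is correct, but the plan states its power at 70%.
- **The sample size text already ties the 59 cases to PPE**, and the protocol has the Endpoint Adjudication Committee (EAC) evaluating each case. Also correct. Only the trigger sentences leave this out, so that part is a matter of wording.

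The estimate, the confidence interval and the control of type I error do not depend on the power statement.

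**Conclusion.** The stated power is wrong as written. At VE 70%, null VE 30%, one-sided 0.025, 1:1 allocation and exactly 59 events, the planned Cox interval criterion has about 80% power (78–81.5% by Wald formula, simulation and exact test). The chance of missing a vaccine with the assumed efficacy is therefore about 20%, not 10%. A modest overrun of the trigger would put it at roughly 79–88%, depending on the exact count and test.

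The conclusion rests on proportional hazards, Wald limits or an exact test as the reading of the model-based interval, and the assumed VE of 70%. The attribution to the 4/D formula is an inference, but the recomputed power does not depend on it. The difference between the two trigger sentences is real but minor.

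**What to change.** Choose one of two corrections and make it in both the synopsis and SAP 4.3:

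- **Keep 59 events** and state the power as about 80% at VE 70%, naming the method and the expected split of about 14 to 45 cases. This changes wording only.
- **Keep 90% power** and raise the trigger to about 78 events. That is 19 more cases and no more participants. At the plan's rates, cases accrue at 3,825 × 1.5% × (1 + 0.3) = 74.6 a month, so 19 take about 1 week. At the PPE size in Table S2 the rate is (1,309 + 0.3 × 1,314) × 1.5% = 25.5 a month, or about 3 weeks.

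The second option is open only before unblinding. The Supplementary Appendix already tabulates cases by arm, so if the final analysis has been run, only the restatement remains.

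In either case, replace both trigger sentences with one wording: at least N EAC-confirmed primary endpoint events in PPE. State in SAP 7.6.1 which type of confidence limit is used, since the power depends on it.

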**Statistical populations:**

**Full Analysis Set (FAS):** All randomized participants who received one

dose of the investigational product (IP). Participants will be analyzed according to the treatment group to which they were randomized.

**Per-Protocol Set (PPS):** All participants in the FAS set who received one dose of IP per schedule and have no major protocol deviations, as determined and documented by the Sponsor prior to DBL and unblinding, that could impact critical or key study data. Participants will be analyzed according to the treatment group to which they were randomized.

**Per-Protocol Set for Efficacy (PPE):** Participants in the PPS set who have negative results of nucleic acid test and with total anti-spike antibodies < 338 BAU/mL at baseline, as well as no evidence for SARS-CoV-2 infection (positive results of antigen or nucleic acid test) within 7 days after the study vaccination. Participants in the PPE set are the main analysis population for VE assessment 7 days after the study vaccination.

**Per-Protocol Set for Efficacy-14 (PPE-14):** Participants in the PPS set who have negative results of nucleic acid test and with total anti-spike antibodies < 338 BAU/mL at baseline, as well as no evidence for SARS-CoV-2 infection (positive results of antigen or nucleic acid test) within 14 days after the study vaccination. Participants in the PPE-14 set are the main analysis population for VE assessment 14 days after the study vaccination.

**Safety Set (SS):** All randomized participants who received one dose of IP. The safety analysis will be based on the treatment group to which the participants receive. Individuals who received the study vaccination but were not randomized will be excluded from the safety set, the safety data of them will be listed separately.

**Immunogenicity full analysis set (I-FAS):** All participants in the FAS who had a valid immunogenicity test result prior to receiving IP and at

least 1 valid result after receiving IP.

**Immunogenicity Per-Protocol Set (I-PPS):** All participants in the PPS who had a valid immunogenicity test result prior to receiving IP and at least 1 valid result after receiving IP.

Participants in the PPE set are the main analysis population for VE assessment (including primary endpoint) 7 days after the study vaccination. Participants in the PPE-14 set are the main analysis population for VE assessment 14 days after the study vaccination

Participants in the SS set are the main analysis population for safety.

Participants in the I-PPS set are the main analysis population for immunogenicity. Particularly, participants with evidence of SARS-CoV-2 infection prior to the target date of the analysis (e.g. 28 days after the study vaccination) will be excluded from the immunogenicity analysis.

#### **Statistical analysis methods:**

##### **Efficacy analysis**

Analysis of the primary endpoint will be performed based on PPE.

Primary endpoint: The vaccine efficacy will be estimated with 1-HR using a Cox proportional hazard regression model with separate baseline strata of age (18-59 years,  $\geq 60$  years) and the type of the last dose of COVID-19 vaccine previously received (inactive, non-inactive). Events that coincide in time will be processed based on the Efron method.

Subgroup analysis of the primary efficacy endpoint will be performed to assess the consistency of vaccine efficacy, such as different ages (18-59 years,  $\geq 60$  years), and the type of the last dose of COVID-19 vaccine previously received (inactive, non-inactive).

Details of the sensitivity analysis are described in section 11.4.4.

Similar statistical analysis model will be applied to VE assessment for both the primary endpoint and second endpoints.

**Immunogenicity Analysis**

The Immunogenicity analysis will be based on I-PPS.

The GMT of neutralizing antibody for each group with corresponding 2-sided 95% CI will be estimated.

Comparisons between groups were based on age (18-59 years,  $\geq 60$  years) and the type of last dose of COVID-19 vaccines (inactive, non-inactive) as fixed effects ANOVA model

**Safety Analysis**

Safety analysis will be based on SS.

AEs and SAEs are encoded based on the *Medical Dictionary for Regulatory Activities* (MedDRA), and also based document the classified statistics were made according to the system organ class (SOC) and preferred term (PT). In this trial, the solicited adverse events (both systemic and local ) will be summarized and classified according to PT.

In this trial, the treatment emergent adverse events (TEAEs) will be summarized, and the adverse medical conditions occurring before the study vaccination are listed. Unless otherwise specified, the adverse events as described below are TEAEs.

The number of occurrences, number of cases and incidence rate of AEs, SAEs and AESIs in each group will be summarized respectively. The adverse events related to the study vaccine, SAEs and AESIs will be listed.

Supplemental analysis will be performed on adverse events in the following populations:

- Participants who have negative results of PCR test at baseline and negative results of rapid antigen test on Day 7;
- Participants who have negative results of PCR test at baseline and negative results or absence of rapid antigen test on Day 7;

- Participants who have positive results of PCR test at baseline.

### **Multiplicity**

A fixed sequence hierarchical procedure will be followed to have the overall Type I error rate controlled at one-sided 0.025. The subsequent test will be performed as follows:

- 1) Primary endpoint: among the population in PPE, VE for symptomatic SARS-CoV-2 infection 7 days ( $\geq 8$  days) after the study vaccination is higher than 30%;
- 2) Secondary endpoint: among the population in PPE, VE for obvious symptomatic SARS-CoV-2 infection 7 days ( $\geq 8$  days) after the study vaccination is higher than 0%;
- 3) Secondary endpoint: among the population in PPE, VE for all infections of SARS-CoV-2 (including symptomatic and asymptomatic infection of SARS-CoV-2) 7 days ( $\geq 8$  days) after the study vaccination is higher than 0%;
- 4) Secondary endpoint: among the population in PPE-14, VE for symptomatic infection of SARS-CoV-2 14 days ( $\geq 15$  days) after the study vaccination is higher than 0%;
- 5) Secondary endpoint: among the population in PPE-14, VE for obvious symptomatic infection of SARS-CoV-2 14 days ( $\geq 15$  days) after the study vaccination is higher than 0%;
- 6) Secondary endpoint: among the population in PPE, VE for asymptomatic infection of SARS-CoV-2 7 days ( $\geq 8$  days) after the study vaccination is higher than 0%;
- 7) Secondary endpoint: among the population in PPE, VE for obvious symptomatic infection of SARS-CoV-2 7 days ( $\geq 8$  days) after the study vaccination is higher than 30%;
- 8) Secondary endpoint: among the population in PPE, VE for all infections of SARS-CoV-2 7 days ( $\geq 8$  days) after the study vaccination is higher than 30%;
- 9) Secondary endpoint: among the population in PPE-14, VE for symptomatic infection of SARS-CoV-2 14 days ( $\geq 15$  days) after the study vaccination is higher than 30%;

|                                                     |                                                                                                                                                                                                                                                                                                                                                                                                                                                                                                                                                                                                                                                                                                                                                                    |
|-----------------------------------------------------|--------------------------------------------------------------------------------------------------------------------------------------------------------------------------------------------------------------------------------------------------------------------------------------------------------------------------------------------------------------------------------------------------------------------------------------------------------------------------------------------------------------------------------------------------------------------------------------------------------------------------------------------------------------------------------------------------------------------------------------------------------------------|
|                                                     | 
10) Secondary endpoint: among the population in PPE-14, VE for obvious symptomatic infection of SARS-CoV-2 14 days (<math>\geq 15</math> days) after the study vaccination is higher than 30%.
 
Interim and final analysis
 
The is no planned interim analysis in this study. The final analysis will be performed for the primary endpoint at the significance level of 0.025 unilateral when more than 59 primary endpoint cases have been collected. The final analysis will be performed by an independent third party, the sponsor will set up an unblinded team for delivery. Investigators, participants and team members directly involved in this study will remain blinded for long-term efficacy and safety follow-up.
 |
| Independent Data Monitoring Committee (IDMC) | 
The sponsor will establish the IDMC to review the safety data of the clinical trials. The IDMC members include experts in the field of vaccine clinical trials, biostatisticians and epidemiologists. See the "IDMC charter" for details of its working documents.
                                                                                                                                                                                                                                                                                                                                                                                                                                                                                          |
| Endpoint Adjudication Committee (EAC)        | 
Endpoint Adjudication Committee (EAC) will be set up in this phase III study to conduct independent evaluation and judgment for each case, to ensure a more accurate determination of the positive cases.
                                                                                                                                                                                                                                                                                                                                                                                                                                                                                                                                                   |

Table 1 Schedule of Activities

|                                                                                    | Screening period | Vaccination                                                                                                                                                                                                | Follow-up period                                                                                                        |         |         |          |          | Blinded or unblinded determined by the participant | Follow-up period |
|------------------------------------------------------------------------------------|------------------|------------------------------------------------------------------------------------------------------------------------------------------------------------------------------------------------------------|-------------------------------------------------------------------------------------------------------------------------|---------|---------|----------|----------|----------------------------------------------------|------------------|
| Visit                                                                              | V1               | V2                                                                                                                                                                                                         | V3                                                                                                                      | V4      | V5      | V6&      | V7&      | V8^                                                | V9/EOS^          |
| Planned visit date                                                                 | D-7~D0           | D0                                                                                                                                                                                                         | D7                                                                                                                      | D14     | D28     | D90      | D180     | After the final efficacy analysis                  | D365             |
| Visit window period                                                                | /                | /                                                                                                                                                                                                          | +2 days                                                                                                                 | ±3 days | +7 days | ±10 days | ±10 days | /                                                  | ±10 days         |
| Management and general procedure                                            |                  |                                                                                                                                                                                                            |                                                                                                                         |         |         |          |          |                                                    |                  |
| Signing the informed consent form                                                  | •                |                                                                                                                                                                                                            |                                                                                                                         |         |         |          |          |                                                    |                  |
| Assigning the screening number                                                     | •                |                                                                                                                                                                                                            |                                                                                                                         |         |         |          |          |                                                    |                  |
| Confirm participant meets inclusion and exclusion criteria             | •                | •*                                                                                                                                                                                                         |                                                                                                                         |         |         |          |          |                                                    |                  |
| Demographic data                                                       | •                |                                                                                                                                                                                                            |                                                                                                                         |         |         |          |          |                                                    |                  |
| Recording the medical history                                          | •                |                                                                                                                                                                                                            |                                                                                                                         |         |         |          |          |                                                    |                  |
| Nasal/pharyngeal/throat swab rapid antigen test for SARS-CoV-2  | •                |                                                                                                                                                                                                            | •                                                                                                                       | •       |         |          |          |                                                    |                  |
| Nasal/pharyngeal/throat swab nucleic acid test for SARS-CoV-2   | •                | •*                                                                                                                                                                                                         | The sample will be collected from the participants who have COVID-19 related signs/symptoms, reference to Section 9.3.4 |         |         |          |          |                                                    |                  |
| Vital signs                                                            | •                | •*                                                                                                                                                                                                         |                                                                                                                         |         |         |          |          |                                                    |                  |
| Physical examination                                                   | •                |                                                                                                                                                                                                            |                                                                                                                         |         |         |          |          |                                                    |                  |
| Anti-SARS-CoV-2 IgG antibodies                                         | •                |                                                                                                                                                                                                            |                                                                                                                         |         |         |          |          |                                                    |                  |
| HIV testing (not applied in China)                                                 | •                |                                                                                                                                                                                                            |                                                                                                                         |         |         |          |          |                                                    |                  |
| Urine pregnancy test (for women of childbearing potential only)        | •                | •*                                                                                                                                                                                                         |                                                                                                                         |         |         |          |          |                                                    |                  |
| Confirmation the selection of participants                             |                  |                                                                                                                                                                                                            |                                                                                                                         |         |         |          |          | •                                                  |                  |
| Randomization                                                                      |                  | •*                                                                                                                                                                                                         |                                                                                                                         |         |         |          |          |                                                    |                  |
| Vaccination                                                                        |                  | •                                                                                                                                                                                                          |                                                                                                                         |         |         |          |          |                                                    |                  |
| Immunogenicity follow-up                                                    |                  |                                                                                                                                                                                                            |                                                                                                                         |         |         |          |          |                                                    |                  |
| Neutralizing antibodies test                                          |                  | •                                                                                                                                                                                                          | •                                                                                                                       | •       | •       | •        | •        |                                                    | •                |
| Efficacy follow-up visit                                                    |                  |                                                                                                                                                                                                            |                                                                                                                         |         |         |          |          |                                                    |                  |
| Efficacy follow-up                                                                 |                  | The follow-up visit will be conducted once a week by means of phone call, text message, e-mail or on site. On-site visit will only be conducted when investigators think it is necessary. The frequency of |                                                                                                                         |         |         |          |          |                                                    |                  |

|                                                                           | Screening period | Vaccination | Follow-up period |         |         |                     |                     | Blinded or unblinded determined by the participant | Follow-up period    |
